### Study schedule

Screening visit. All patients will undergo screening within the 4 weeks prior to the baseline visit (see section ‘Screening’ above).Baseline visit (week 0). This visit will be performed to confirm eligibility for the study and for randomisation and initiation of study treatment.Assessment and treatment visits. These visits will be performed at weeks 4, 12 and every 12 weeks thereafter, up to week 96, for both treatment arms.Additional visits (for treatment arm 2). The patients in treatment arm 2 will also be monitored at week 8, 16 and 20 for safety and efficacy within a TT protocol. In patients switching to ETN and MTX at week 24 a follow up safety visit will be arranged 4 weeks following ETN commencement (i.e. week 28).

### Methods of assessment

#### Clinical efficacy

Clinical efficacy and remission will be assessed by the following measures, with joint examinations performed by the same blinded assessor.

*DAS44 and DAS28*, based on the evaluation of four variables: tender joint assessment (Ritchie Articular Index, RAI, and 28 joint count respectively), number of swollen joints (out of 44 and 28, respectively), erythrocyte sedimentation rate (ESR; mm/h) and patient’s global assessment of arthritis, as assessed by a 100 mm visual analogue scale (VAS). These will be performed at each visit for both treatment arms. The scores will be calculated using the following formulae: DAS28 = 0.56*sqrt (tender28) + 0.28*sqrt(swollen28) + 0.70*ln(ESR) + 0.014*VAS; DAS 44 = 0.54*sqrt(RAI) + 0.065*(swollen 44) + 0.33*ln(ESR) + 0.0072*VAS. Remission thresholds for DAS44 and DAS28 are <1.6 and <2.6 respectively [26].

*CDAI* is the sum of four variables: number of tender and swollen joints (out of 28), the investigator’s global assessment of disease activity and the patient’s global assessment of arthritis assessed by VAS (cm). The threshold for CDAI remission is <2.8 [27].

*SDAI* is the CDAI plus CRP (mg/dL). The threshold for SDAI remission is <3.3 [28].

*EULAR response criteria* classify patients as good, moderate or non-responders based on a combination of the actual DAS and change from previous DAS [29].

*ACR response* measures 20 % (ACR20), 50 % (ACR50) or 70 % (ACR70) improvement in tender and swollen joint counts and in at least three of the following parameters: patient global assessment, physician global assessment, pain, disability and acute phase reactant (ESR or CRP) [30].

*The physician global assessment* of rheumatoid disease activity should be completed before the patient’s global assessment is received. The investigator will mark their assessment on a 100 mm visual analogue scale (VAS): the left end corresponds to none (0) and the right end to extremely active (100).

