#### Secondary objectives

To assess the change in MRI synovitis between baseline and 48 weeks following very early ETN or MTX-TT regimen +/- delayed ETN.To evaluate other clinical efficacy endpoints at weeks 12, 24, 48 and 96 including:✓ Disease activity score-44 joint (DAS44) remission (DAS44 < 1.6), simplified disease activity index (SDAI), clinical disease activity index (CDAI), European League Against Rheumatism (EULAR) response criteria, American College of Rheumatology (ACR) response criteria.✓ Cumulative steroid dose.To evaluate patient-reported outcomes at weeks 12, 24, 48 and 96 including:✓ Physical function, assessed by the Health Assessment Questionnaire (HAQ), including normalisation of HAQ.✓ Quality of life scores assessed by RA Quality of Life (RA-QoL) and Euro QoL Five Dimensions (EQ-5D) questionnaires.✓ Work instability, assessed by RA Work Instability Score (RA-WIS) questionnaire.To evaluate imaging predictors of remission and sustained remission using:✓ High-resolution ultrasound (HRUS) at weeks 0, 12, 24 and 48 measuring grey scale (GS), PD and presence or absence of erosions.✓ Magnetic Resonance Imaging (MRI) at weeks 0, 12, 24 and 96 measuring synovitis and erosion scores.To evaluate other radiographic outcomes including:✓ Joint damage assessed by modified Sharp score of X-rays of hands and feet at weeks 48 and 96.

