### Randomisation

Once eligibility is confirmed and all relevant procedures have been completed, participants will be block randomised 1:1 to one of the following two treatment groups (Fig. 1):Treatment Arm 1 or ‘very early ETN’ will receive ETN and MTX combination therapy administered for a total duration of 48 weeks.Treatment Arm 2 or ‘delayed ETN’ will receive initial MTX monotherapy with adoption of a TT protocol (standard care involving monthly DAS28-ESR assessment with escalation to combination sDMARD therapy if not achieving LDA at, or after, 8 weeks) and step-up to ETN and MTX at 24 weeks if failing to achieve clinical remission.

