#### Treatment arm two

In treatment arm two (Table 2), MTX will be administered orally at a starting dose of 15 mg and will be increased to 25mg weekly at 2 weeks. Subcutaneous MTX may be administered if intolerance to oral MTX is observed. If at weeks 8, 12, 16 or 20, the subject fails to achieve LDA (defined as DAS28-ESR ≤ 3.2), sulfasalazine (SSZ) and hydroxychloroquine (HCQ) will be added to MTX. SSZ will be administered orally at a dose of 1g twice daily (or at the maximum tolerated dose). HCQ will be administered at a dose of 200mg daily. At 24 weeks, if a subject fails to achieve clinical remission, ETN will be added to MTX, and SSZ and HCQ will be discontinued (if applicable).

#### Treatment arms 1 and 2

Oral folic acid will be administered at a dose of 5mg daily (except on the day of MTX) to subjects in both treatment arms.

ETN will be discontinued in both arms at the primary endpoint (48 weeks), with the exception of those patients who are eligible to continue according to local prescribing guidelines (NICE guidelines) [15].

A single non-steroidal anti-inflammatory drug (NSAID) is permitted providing the dose has been unchanged for at least 28 days prior to study drug initiation at baseline. The NSAID or NSAID dose may be changed during the time course of the study if indicated.

Oral prednisolone is permitted at doses up to and including 10mg prednisolone daily if the dose has been stable for at least 28 days prior to study drug initiation at baseline. The steroid dose may be reduced throughout the study.

Intramuscular steroid may be administered as per the study treatment protocol for each arm with all patients receiving 120mg intramuscular methylprednisolone (unless contraindicated or not tolerated) at baseline and at the following time-points according to treatment arm and disease activity:Week 12: both treatment arms, if DAS28-ESR > 3.2Week 24: treatment arm 1, if DAS28-ESR ≥ 2.6 (treatment arm 2 switch to ETN+/-MTX if DAS28-ESR ≥ 2.6)Week 36:✓ Treatment arm 1, if DAS28-ESR≥2.6✓ Treatment arm 2, sDMARDs (MTX +/-SSZ +/-HCQ), if DAS28-ESR≥2.6✓ Treatment arm 2, switched to ETN+/-MTX, if DAS28-ESR>3.2Up to the primary endpoint (week 48), for a patient with active disease who is judged by the physician to be in need of rescue therapy, and for whom it is considered to be unethical to wait until the 12, 24 and 36 week time points above, 120mg methylprednisolone may be administered.

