Early morning stiffness, HAQ, RA QoL, EQ-5D, RA-WIS		X			X			X		X		X		X	X

a. Visits at weeks 8, 16 and 20 are only applicable to patients in treatment arm 2. b. Cardiovascular risk factors include: smoking habit (pack years), alcohol intake (units/week), amount of exercise taken, dietary intake (days/week ≥ 5 portions fruit or vegetables consumed), and family history of premature cardiovascular disease age <55 years. c. Physical examination Includes height and body weight at screening. d. Blood pressure after a 5-min rest, pulse rate and body temperature e. Urinary pregnancy test for women of child bearing potential only f. Chest x-ray, if not already performed within 24 weeks prior to the study. TB testing includes TB Gold Quantiferon +/- T spot test +/- Mantoux test. g. Whenever possible, joint assessments should be performed by the same blinded assessor throughout the time course of the study to reduce potential investigator bias

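### The same-assessor preference for joint counts, combined with counts scheduled in arm 2 only, lets the week-48 assessor infer that a patient is in arm 2

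*Protocol article*

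**What the plan says.** On who examines the joints, the Clinical efficacy section is unqualified: "Clinical efficacy and remission will be assessed by the following measures, with joint examinations performed by the same blinded assessor". Table 3, footnote g, attached to the DAS28/44 joint assessment row, is softer but covers the whole study: "Whenever possible, joint assessments should be performed by the same blinded assessor throughout the time course of the study to reduce potential investigator bias".

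On when joints are examined, Table 3, footnote a states: "Visits at weeks 8, 16 and 20 are only applicable to patients in treatment arm 2". The DAS28/44 row has an entry at each of those weeks, and its week-4 cell is limited to arm 2.

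On what the counts are for, the Randomisation section describes the arm 2 regimen as "standard care involving monthly DAS28-ESR assessment with escalation to combination sDMARD therapy if not achieving LDA at, or after, 8 weeks". The section on treatment arm two makes the addition of SSZ and HCQ depend on it: "If at weeks 8, 12, 16 or 20, the subject fails to achieve LDA". The secondary objectives place the other "clinical efficacy endpoints at weeks 12, 24, 48 and 96". The primary outcome is DAS28 remission at week 48.

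**The concern.** In an open-label trial the patient's VAS cannot be blinded, and ESR is a laboratory value. The tender and swollen counts are the DAS28 components that a blinded examiner can protect, and footnote g gives reduction of investigator bias as its reason.

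Two stated rules pull against each other. One keeps the same examiner with the patient throughout. The other brings only arm 2 patients to be examined at certain weeks. The better continuity is kept, the more often the week-48 examiner has met arm 2 patients at visits that arm 1 does not have. At stake is the blinding of the counts that enter the primary endpoint, and also DAS44, SDAI, CDAI, EULAR and ACR response.

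**Working it through.** **Inputs.** 120 patients randomised 1:1, so 120 / 2 = 60 per arm (Study design; Sample size). Timing of counts: DAS28/44 row of Table 3 with footnote a. Uses of the counts: Trial intervention, treatment arms 1 and 2. DAS28 formula and the remission threshold of 2.6: Clinical efficacy. The plan gives no figure of its own on this point to reproduce.

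**Step 1: the schedule after baseline.**

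| Week | Arm 1 | Arm 2 | Stated use |
|---|---|---|---|
| 4 | no (table cell) | yes | monthly arm 2 monitoring |
| 8 | no | yes | SSZ/HCQ decision |
| 12 | yes | yes | SSZ/HCQ decision (arm 2), steroid rule, endpoint |
| 16 | no | yes | SSZ/HCQ decision |
| 20 | no | yes | SSZ/HCQ decision |
| 24 | yes | yes | ETN decision (arm 2), steroid rule (arm 1), endpoint |
| 36 | yes | yes | steroid rule |
| 48 | yes | yes | primary endpoint |

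Before week 48, arm 1 has weeks 12, 24 and 36 = 3 counts. Arm 2 has weeks 4, 8, 12, 16, 20, 24 and 36 = 7 counts. The difference is weeks 4, 8, 16 and 20 = 4 counts.

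**Step 2: volume.** 4 × 60 = 240 counts in arm 2 only. Leaving out week 4, 3 × 60 = 180.

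**Step 3: what the examiner can infer.** No arm 1 patient has a scheduled joint count at weeks 8, 16 or 20. An examiner who sees a patient then, and knows the study week, can infer arm 2. Footnote g does not exempt those weeks: it sits on the row that contains them and extends to week 48.

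**Step 4: why one joint can matter.** In the plan's formula the joint terms are 0.56 × √(tender) + 0.28 × √(swollen).
- One tender joint against none: 0.56 × (1 − 0) = 0.56.
- One swollen joint against none: 0.28 × (1 − 0) = 0.28.

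A judgement on a single joint can therefore move a patient who is near 2.6 across the threshold.

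**Step 5: a comparator within the plan.** The Imaging assessments section has a blinded assessor perform ultrasound at baseline and weeks 12, 24 and 48, with no visits for one arm only. That schedule reveals nothing about the arm.

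**The case against.** **The wording does not compel the exposure.** Footnote g asks for a blinded assessor only whenever possible. A visit that would reveal the arm can be read as a case where it is not possible, and the monthly arm 2 DAS28 is described as standard care. This stands in part: handing those visits to other staff would already comply. But the footnote names the same assessor as the preferred case on a row that includes those weeks, so the text is at best ambiguous.

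**The full protocol may describe masking.** This also stands. A reader might infer that the trial has no masking of the visit pattern, or that the assessor is certain to be unblinded. A condensed article supports neither. The point is limited to what the two stated rules do together.

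**Arm is not drug.** The Sample size section expects about half of arm 2 to receive ETN from week 24, so an examiner who infers arm 2 does not know the drug at week 48. True, but the primary comparison is between arms, and knowing the arm is enough to tilt it.

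**A number of affected patients.** A reader might want to know how many arm 2 patients the week-48 examiner has met at a revealing visit. The document does not say how often continuity is kept, and an assumed share does not settle it. If that examiner made a quarter of the 240 counts (60), these could be all four counts in 15 patients or one count in each of 60. No useful figure follows.

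**Week 4.** The text says of DAS28 and DAS44 "These will be performed at each visit for both treatment arms", and week 4 is a visit for both arms, yet the table limits its DAS to arm 2. A reader might count this as a separate error. It is editorial: no stated endpoint or decision uses an arm 1 week-4 DAS28. Its only effect here is whether the arm-2-only total is 240 or 180.

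**Conclusion.** The point holds as a weakness in the blinding of the joint counts, and is worth a cheap change. Followed as written, the same-assessor preference lets the person who makes the week-48 counts infer that a patient is in arm 2. The size of the opportunity is 7 joint counts against 3 per patient before week 48: 240 arm-2-only counts by the table cells, or 180 for weeks 8, 16 and 20 alone.

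This rests on three assumptions: the examiner knows the study week, arm 1 patients are not examined at those weeks outside the schedule, and no masking step exists beyond the text shown. The document gives no basis for a size or direction of bias or for an inflated false-positive rate, and none is claimed. Two of the four DAS28 components do not depend on the examiner.

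**What to change.** In the Clinical efficacy section and in footnote g, state that the blinded assessor, the same one whenever possible, makes the joint counts at the weeks scheduled for both arms (0, 12, 24, 36, 48 and later). State also that the treating team makes the arm-2-only treat-to-target counts (weeks 8, 16 and 20, and week 4 as the table has it) and does not show them to that assessor.

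If this cannot be done for a visit, record the assessor's code with each count. Then report how many week-48 counts came from someone who had examined that patient at an arm-2-only visit. The route to inference through these visits closes fully only if the change is made in full; partial use reduces it.

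The cost is a few sentences, and one code per form in the fallback. No visit, joint count or blood test is added, because the arm 2 counts are already planned. The week-12 count and the week-24 count that decides ETN stay with the blinded assessor. The downside is that the SSZ/HCQ decision at weeks 8, 16 and 20 may rest on a different examiner from week 12, which footnote g already permits.

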### Study design

The VEDERA study is a phase IV single-centre open-label randomised trial of 120 patients with early, treatment-naive RA. Patients will be randomised 1:1 to first-line ETN and MTX or MTX with additional sDMARDs and step up to ETN and MTX after 24 weeks as required according to a TT protocol aiming for remission.

The randomised trial duration is 48 weeks after which ETN will be stopped and patients will continue for a 48-week observational period during which DMARDs will be used as per standard care, in accordance with national guidelines.

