#### Exploratory biosample based research

Blood samples will be collected at baseline and weeks 12, 24, 36, 48, 96, at time of early discontinuation (if indicated) and at time of flare (if indicated). This will include collection of serum, plasma and heparinised blood (for flow cytometry and functional studies).

Synovial biopsy (optional) will be taken from a target joint: an active joint (identified at baseline by presence of PD activity on ultrasound) or alternatively, if necessary, a clinically uninvolved, accessible joint may be chosen. The optional biopsy will be acquired via arthroscopy or under ultrasound guidance at baseline and week 24; at week 48 in patients randomised to treatment arm 2 receiving delayed ETN from week 24, and at time of flare in the case of loss of response in an initial responder. Failure of biopsy acquisition at any time point will not constitute a protocol violation and will not necessitate withdrawal from the study.

The sample collection will be used for wide-ranging studies including cellular phenotyping, soluble biomarker evaluation and gene expression studies.

A detailed study schedule is provided in Table 3.

**Table 3 Tab3:** Study schedule

				Arm 2^a^		Arm 2^a^	Arm 2^a^								
Study Week	Weeks -4 to 0	Week 0	Week 4	Week 8	Week 12	Week 16	Week 20	Week 24	Week 36	Week 48	Week 60	Week 72	Week 84	Week 96	Early discontinuation
Study Phase	Screen	Baseline	Safety visit							1^0^ Endpoint				End of Study	
Visit No.	1	2	3	4	5	6	7	8	9	10	11	12	13	14	
Informed Consent (patient information will be provided > 24 hrs prior to screen)	X														
Inclusion/exclusion criteria	X	X													
Randomisation		X													
Demographics, RA Hx, past medical Hx, Family Hx, CV risk factors^b^	X														
Physical examination^c^	X				X										X
Vital signs^d^	X	X	X		X			X	X	X	X	X	X	X	X
Pregnancy test^e^	X	X													
ESR, CRP and HS-CRP	X	X	X (Arm 2 only)	X	X	X	X	X	X	X	X	X	X	X	X
Blood chemistry, haematology	X	X	X	X	X	X	X	X	X	X	X	X	X	X	X
Urinalysis	X	X	X		X			X		X		X		X	X
Serology: RF, ACPA and ANA	X													X	X
ECG	X														
Chest x-ray/TB test^f^	X														
Hepatitis (B and C) serology	X														
VAS assessments: patient general health, patient global, patient pain	X	X	X (Arm 2 only)	X	X	X	X	X	X	X	X	X	X	X	X
Physician VAS global disease activity	X	X			X			X		X		X		X	X
DAS_28/44_ joint assessment^g^	X	X	X (Arm 2 only)	X	X	X	X	X	X	X	X	X	X	X	X

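### The physician global that enters CDAI, SDAI and ACR response is assigned to the investigator in an open-label trial, with no stated protection from knowledge of the arm

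*Protocol article*

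**What the plan says.** The Study design section describes a "phase IV single-centre open-label randomised trial of 120 patients". Under Methods of assessment, Clinical efficacy, the clinical measures are to be taken "with joint examinations performed by the same blinded assessor". Footnote g to Table 3 repeats this for the joint assessment row: "Whenever possible, joint assessments should be performed by the same blinded assessor throughout the time course of the study to reduce potential investigator bias". The ultrasound assessor is also described as blinded. No other clinical rating is.

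The physician global is dealt with separately in the Clinical efficacy section: "The investigator will mark their assessment on a 100 mm visual analogue scale (VAS". Its one safeguard is that it "should be completed before the patient’s global assessment is received". In Table 3 it has its own row, "Physician VAS global disease activity", which does not carry footnote g.

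The rating is then used in three endpoints. CDAI adds the 28-joint tender and swollen counts to "the investigator’s global assessment of disease activity and the patient’s global assessment of arthritis assessed by VAS (cm", with remission below 2.8. SDAI is CDAI plus CRP in mg/dL, with remission below 3.3. ACR response needs improvement in both joint counts and in at least three of five further items, one of which is the physician global. The Secondary objectives list "simplified disease activity index (SDAI), clinical disease activity index (CDAI" and ACR response among the clinical efficacy endpoints at weeks 12, 24, 48 and 96.

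**The concern.** In an open-label trial a blinded assessor protects only the ratings that the assessor makes. Here that protection is stated for the joint counts but not for the other clinician-rated term, which is a global impression and so the more open to expectation. The stated safeguard keeps the physician's mark independent of the patient's score. It does nothing about knowledge of the arm.

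These endpoints are not merely descriptive. The Secondary efficacy analyses section has binary responses compared between arms by Pearson's chi-squared test, and the Discussion treats the secondary outcomes as supportive of the primary hypothesis. If the rater knows the arm and expects first-line etanercept to do better, CDAI, SDAI and ACR response could agree with the DAS28 result partly for that reason.

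**Working it through.** The plan states no figure on rater bias, so there is none to reproduce. The check has four parts.

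**1. Who rates, and blinded to what.** The passages compare as follows:
- Joint counts: blinded assessor (Clinical efficacy; footnote g adds that this applies whenever possible).
- Physician global: the investigator; no statement on blinding; no footnote g on its Table 3 row.
- Purpose of the blinded assessor in footnote g: to reduce investigator bias. That names the investigator as the source of bias and the blinded assessor as the remedy, which points to two roles. No sentence says outright that they are two people or that the investigator knows the arm.

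**2. What the mark can do in CDAI and SDAI.** Let P be the physician mark in cm (mm divided by 10) and R the sum of the other components.
- CDAI remission: R + P < 2.8, where R is tender count + swollen count + patient global in cm.
 - R = 0: P must be below 2.8, so a mark of 28 mm or more denies remission.
 - R = 1.0: 2.8 − 1.0 = 1.8, so the mark must be below 18 mm.
 - R = 2.0: 2.8 − 2.0 = 0.8, so the mark must be below 8 mm.
 - R ≥ 2.8: remission is impossible at any mark, including 0.
- SDAI remission: R + P < 3.3, where R now also includes CRP. With R = 0, a mark of 33 mm or more denies remission.

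The mark alone can therefore deny remission. It can confer remission only on a patient whose other components are already below the threshold. A shift of d mm changes a patient's CDAI class only if the total lies within d/10 of 2.8. For a 5 mm shift, that means totals from 2.3 up to 2.8 if the mark rises, or from 2.8 up to 3.3 if it falls and the original mark was high enough to allow the fall. The documents do not say how many patients lie in that band.

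**3. What it can do in ACR response.** Both joint counts must have improved, and three of five items are needed. The physician global is pivotal only when exactly two of the other four items are met: C(4,2) = 6 of 2⁴ = 16 patterns. This counts patterns and is not a probability.

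**4. What a spurious difference would do to a test (assumptions, not document figures).** Take 60 per arm as planned, true remission of 40 % in both arms, and a rating-induced difference δ split evenly, so p₁ = 0.40 + δ/2 and p₂ = 0.40 − δ/2. The two-sided 5 % critical difference is 1.96 × √(2 × 0.40 × 0.60 / 60) = 0.175. The rejection probability is 1 − Φ[(0.175 − δ)/SE] + Φ[(−0.175 − δ)/SE], with SE = √{[p₁(1 − p₁) + p₂(1 − p₂)]/60}.
- δ = 0: 5 %.
- δ = 0.05: SE = 0.0893, about 9 %.
- δ = 0.10: SE = 0.0890, about 20 %.
- δ = 0.15: SE = 0.0884, about 39 %.

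These rates are before the Holm correction, which lowers the threshold for a test but does not remove a bias.

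**Feasibility of the remedy.** Table 3 schedules the physician global at screening, weeks 0, 12, 24, 48, 72 and 96, and at early discontinuation. The joint assessment is scheduled at every one of these visits.

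**The case against.** The strongest reply is that the separate, unblinded rater is inferred. The article never says that the investigator differs from the blinded assessor or knows the arm, and a full protocol may settle it. That stands as a limit on how firmly the point can be put. It does not reduce the point to missing detail, because the article does say who marks the scale, on what scale and in what order relative to the patient's score. A safeguard was chosen, and it is not the one that an open-label design calls for.

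The second reply is that patient global stays open-label in all three endpoints, as do pain and disability in ACR response, and that patient global also enters the primary DAS28. That is true and the fix does not change it. But patients who know their treatment cannot be blinded, whereas this clinician rating can be.

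The third reply is that the affected measures are some of many secondary outcomes, under Holm correction, in a trial described as pragmatic. This bears on priority and stands.

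A reader might also infer more than the documents support:
- That the mark settles remission by itself in either direction. It can only deny it, and a mark of 28 mm in a patient with no tender or swollen joints and a patient global of 0 is an extreme case.
- That the same holds for ACR response. That is a response criterion with five items, not a remission criterion.
- That the rating investigator also makes the treatment decisions. The text leaves discretion to the physician and ties the main escalation steps to DAS28-ESR cut-offs.
- That the bias has a known size. The documents give no CDAI distribution, no spread of physician marks and no expected shift between arms.

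**Conclusion.** The point holds in limited form. The article states blinding for the joint examinations, assigns the physician global to the investigator, and gives that rating no protection from knowledge of the arm. That the rater is not the blinded assessor is a strong inference from the wording, not a stated fact.

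The consequence is confined to CDAI, SDAI and ACR response. The DAS28 and DAS44 formulae contain no physician global, and EULAR response is built on the DAS, so the primary result is untouched by this route. Within CDAI and SDAI the mark matters for patients near the threshold; within ACR response it is only sometimes pivotal. The size of any bias cannot be taken from the documents. The rejection rates of about 9 %, 20 % and 39 % follow from assumed differences of 5, 10 and 15 points and an assumed 40 % remission in both arms. They show what such differences would do, not that they will arise. The change is worth making because this route to bias can be avoided at little cost.

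**What to change.** In the Clinical efficacy section, state that the blinded joint assessor marks the global disease-activity scale used in CDAI, SDAI and ACR response, straight after the joint examination and without access to treatment notes. Keep the existing rule that it precedes receipt of the patient's global, and extend footnote g to the physician global row of Table 3. Any treating-physician rating may be recorded but should not enter these endpoints.

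If the blinded assessor cannot rate it, say who does and whether that person is blinded, and add a sensitivity analysis of the three endpoints without the physician global. That analysis needs its rule set in advance. Dropping a term lowers the CDAI and SDAI totals, so keeping 2.8 and 3.3 would make remission easier to reach, and ACR response would need a stated number out of the four remaining items.

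No visit or extra staff member is needed, since the joint assessment is already scheduled whenever this scale is marked. The downside is that the blinded assessor rates overall activity with less clinical history than the investigator may have.
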